### Plans to give access to the full protocol, participant-level data, and statistical code

The study protocol has been published on www.coptrin.dk.

Participant-level data and statistical code will not be published.

### Composition of the data monitoring committee, its role, and reporting structure

The DSMB comprises three independent members who will assess the interim analysis 6 months after the recruitment of the last patient.

### Adverse event reporting and harms

N/A as the trial does not alter the type of medication or dosage of medication already being used.

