## Introduction

### Background and rationale

One of the most serious complications of chronic obstructive pulmonary disease (COPD) is acute exacerbation (AECOPD). On average, each COPD patient experiences 0.5–3.5 acute exacerbations per year, which is an important reason for hospitalization, disease progression, and mortality as well as a decline in health status and lung function (1, 2). Treatment with a long-acting muscarinic antagonist (LAMA) reduces dyspnea and the risk of exacerbations in patients with COPD by binding to muscarinic receptors in bronchial smooth musculature and thus inhibiting cholinergic bronchial constriction. LAMAs are given as inhalation therapy once daily (most often) or twice daily (3). Most COPD patients experience their worst symptoms and experience exacerbations in the early morning hours, before getting out of bed (4). This might be explained by the physiological diurnal changes in the activity of the parasympathetic homeostasis system, which is most active at night to improve digestion and other secretions (5). Correspondingly, the activity of the sympathetic system is physiologically suppressed at night, and stimulation of β-2 receptors is thus also low (and opposite for M-3 receptors). The balance of sympathetic-parasympathetic tone is shifted significantly toward the latter. Most available LAMA treatments are dosed once daily in the morning. Thus, for a COPD patient, being at a trough level of LAMA (which antagonizes the parasympathetic system) at late night/early morning, may carry a hazard for the patient. Studies have found that lung function measured as a forced expiratory volume in 1 s (FEV1) improvement peaks approximately 2 h after LAMA administration and that FEV1 is still significantly improved at 7 h post-treatment but decreases toward the trough level of the LAMA (6). However, as a corollary to the above, when the medicine is probably most needed (02.00 a.m.–07.00 a.m.), the effect is at its lowest level, which may not be desirable, since a low effect of the most important preventive medicine against AECOPD at this time may lead to more exacerbations. Evening administration, on the contrary, would lead to a greater and more certain effect regarding bronchodilation and reduced secretion in the early morning hours, and a maximum effect should be expected during the entire night.

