### Eligibility criteria

Inclusion criteria:

Age > 30 years.Current treatment with LAMA once daily (as recorded in the Danish National Prescription Registry and confirmed by the participant via questionnaire).Confirmed COPD diagnosis.

Exclusion criteria:

Patients who decline to participate.

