## Interventions

### Explanation for the choice of comparators

Patients will be randomized 1:1 to one of the two treatment strategies by computer-generated allocation to either:

LAMA administration in the morning (control).LAMA administration in the evening (intervention).

These treatment strategies have been chosen because morning administration is the most conventional, while evening administration will be investigated to determine if it is superior with respect to the occurrence of hospitalization-requiring AECOPD or death from all causes within 12 months, along with several secondary and exploratory outcomes, as outlined in Table 1.

**Table 1 tab1:** Primary endpoint definition.

Endpoint	ICD-10 codes	Inpatient/outpatient/minimum required length of stay/other criteria
Hospitalization-requiring AECOPD or death from all causes	Hospitalizations: DJ440, DJ441	For hospitalizations: Type A Diagnosis (primary discharge diagnosis). Inpatient and length of stay ≥24 h, or emergency room visits

The time frame is ≥1 day after randomization until the end of the study (12 months). COPD, chronic obstructive pulmonary disease.

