### Intervention description

Participants randomized to LAMA administration [with or without the combination of inhaled corticosteroids (ICSs) and/or long-acting beta-2-agonists (LABAs)] in the evening will be instructed to take their LAMA-containing inhalation between 8 p.m. and 2 a.m.

Participants randomized to LAMA administration (with or without the combination of ICS and/or LABA) in the morning will be instructed to take their LAMA as usual in the morning between 6 and 12 a.m.

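### Harms are ruled out because drug type and dosage are unchanged, but the trial changes timing, and short hospital contacts for causes other than AECOPD enter no listed outcome

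*Protocol article*

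**What the plan says.** Under Adverse event reporting and harms, the entire entry is "N/A as the trial does not alter the type of medication or dosage of medication already being used".

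Intervention description tells the evening arm to "take their LAMA-containing inhalation between 8 p.m. and 2 a.m"; the morning arm "will be instructed to take their LAMA as usual in the morning between 6 and 12 a.m". Any inhaled corticosteroid or long-acting beta-2-agonist in the same inhaler moves with the LAMA.

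Background and rationale builds the trial on timing. It describes the parasympathetic system as one "which is most active at night to improve digestion and other secretions", calls a trough level at that time a possible hazard, and expects evening dosing to give a stronger effect overnight and in the early morning. Sample size turns this into a hypothesised 25% relative reduction in the primary outcome.

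Safety appears in one other place. Interim analyses and stopping guidance plans a single DSMB review, six months after the last recruitment. It uses Z-scores for the primary endpoint and mortality, and says that safety will be judged by setting event rates against the rate assumed for the sample size.

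**The concern.** The stated reason and the stated hypothesis pull in different directions. If moving the dose shifts the drug's effect enough to prevent a quarter of primary events, then unchanged type and dosage cannot by itself show that there is nothing to look for on the harm side.

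At stake is how a favourable result could be read. If evening dosing lowered AECOPD admissions and raised other hospital contacts, the listed outcomes could show the first clearly and the second only in part. A recommendation to change dosing time would then rest on an incomplete account of benefit and harm.

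**Working it through.** **1. Does the reason support the conclusion?** Set side by side:
- Harms section: type and dosage are unchanged, so harms do not apply.
- Eligibility criteria: entry requires "Current treatment with LAMA once daily". Intervention description changes the clock time only. The harms sentence is therefore accurate about type and dosage.
- Background and Sample size: clock time alters the effect, with an assumed 25% relative reduction.

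The premise is true. The step from it to N/A does not follow, because the premise is silent on the one thing the trial changes.

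**2. Which hospital contacts are counted?** From Tables 1 and 2:
- AECOPD as primary diagnosis, inpatient of at least 24 h or emergency visit: primary endpoint.
- Any cause, inpatient of at least 24 h: all-cause hospitalization.
- Any cause, intensive care of at least 24 h: ICU outcome.
- Non-invasive ventilation, and death: own outcomes.
- Non-AECOPD emergency visit: no outcome.
- Non-AECOPD inpatient stay under 24 h: no outcome.

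A contact of the last two kinds shows up only if it also leads to something listed, such as ventilation, death or a counted prescription.

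**3. How large could the netting be?** The plan's own figure first:
- Control risk: 16,000 / 178,000 = 8.99% (printed as 8.9%).
- Diluted relative reduction: 0.25 × 0.844 = 21.1% (printed as 21.3%).
- Absolute reduction: 8.99% × 0.211 = 1.9 percentage points, as stated.

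The Abstract reports 10,013 randomized 1:1, so about 10,013 / 2 ≈ 5,006 per arm. Then 5,006 × 0.019 ≈ 95 fewer participants with a primary event in the evening arm.

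Let A be the fall in participants with an AECOPD stay of at least 24 h, and B the rise in those with other stays of that length. Ignoring people who have both, all-cause hospitalization shows B − A. Any B below A looks neutral or favourable. A is of the order of 95 if the whole assumed reduction falls on such stays. It would generally be smaller, because part of the reduction would be deaths or emergency visits and some participants would be admitted for other reasons anyway.

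**4. Does the DSMB review close the gap?** Its safety sentence compares observed rates with a planning rate for the efficacy endpoint. The Z-scores are naturally between-arm quantities, but they cover only the primary endpoint and mortality. Neither shows non-AECOPD contacts by arm.

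**5. Minor note: the change of dosing time.** With the morning window read as 06:00–12:00 and the evening window as 20:00–02:00, the first interval for a morning user moved to the evening is:
- same day: 12:00 to 20:00 = 8 h, up to 06:00 to 02:00 = 20 h;
- next evening: 8 + 24 = 32 h, up to 20 + 24 = 44 h.

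No pair of times gives 24 h. If 12 a.m. is taken literally as midnight, the windows overlap from 20:00 to 24:00 and 24 h becomes possible. For comparison, consecutive doses within either window may already be 18 to 30 h apart.

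**The case against.** The best defence is that the harms sentence is literally correct and that the plan is not blind to harm. AECOPD emergency visits, ICU stays, ventilation, moderate exacerbations, SABA pick-up, CAT, MRC and sleep could all worsen under evening dosing. Deaths and all-cause admissions are compared by arm, and a net all-cause measure is a legitimate summary of benefit and harm. If AECOPD admissions fell and all-cause admissions did not, the discrepancy would be visible. There is a DSMB, investigators may pause the intervention for safety, and participants can contact staff throughout. Tables by cause could also be run later from the same registries.

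Most of this stands, and it limits the point. It does not remove it: a visible discrepancy would not reveal its cause, short non-AECOPD contacts would still be missing, and tables chosen after the result is known carry less weight.

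A reader might infer more than the document supports:
- **That the harms sentence is false.** It says nothing about timing, so it is insufficient rather than wrong.
- **That safety is not monitored.** The DSMB review and the outcomes above say otherwise.
- **That the mechanism predicts a particular night-time harm.** Background and rationale discusses bronchodilation and secretion and names no such harm.
- **That about 5,000 people had an irregular dose interval.** That figure is the size of the evening arm. The article says "Most available LAMA treatments are dosed once daily in the morning", but gives no baseline share of morning users. The interval occurs once, and instructions may sit in the participant letter, the linked FAQ or the full protocol.

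**Conclusion.** The point holds in a limited form. Unchanged type and dosage does not justify N/A for harms when timing is the intervention and is expected to change the effect. Two gaps follow: short non-AECOPD hospital contacts enter no listed outcome, and all-cause hospitalization nets any excess of other admissions against an expected AECOPD fall of the order of 95 people per arm. The DSMB's safety comparison, as written, does not cover either.

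The 95 rests on the plan's 25% effect and 84.4% adherence, on equal arms of about 5,006, and on the whole reduction falling on stays of at least 24 h. It shows how much could be masked; it does not estimate a harm, and none is shown. The primary analysis is unaffected. The dose interval at the change of time is a side note: it depends on reading 12 a.m. as noon, affects an unknown number of people once, and has no stated link to 12-month risk.

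**What to change.** - Replace N/A with a descriptive comparison by arm, over 12 months, of non-AECOPD hospital contacts (inpatient of any length and emergency room) by primary diagnosis group, from the registries already in use.
- Give the DSMB the same table by arm, alongside the comparison with the planning rate.
- Reword the harms entry to say that type and daily dosage are unchanged but timing is altered, and reconcile it with Background and rationale, Intervention description, and Interim analyses and stopping guidance.
- Clarify the 12 a.m. limit of the morning window. The article does not describe the change from one dosing time to the other; how it is made is for the investigators.

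The cost is protocol wording and a few registry tabulations, with no visits and no new participant contact. The downside is a set of extra tables with many comparisons and no control of multiplicity, so they should be specified before results by arm are seen and labelled descriptive.

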### Frequency and plans for auditing trial conduct

There will be an independent data safety monitoring committee, as mentioned in 21a. Otherwise N/A.

### Plans for communicating important protocol amendments to relevant parties (e.g., trial participants and ethical committees)

If any changes are made, all relevant parties will be informed promptly by mail and through Trial Setting Committee meetings.

### Dissemination plans

Both negative, positive, and inconclusive results will be submitted for publication in peer-reviewed journals and presented at international scientific conferences. Authorship criteria will be based on Recommendations for the Conduct, Reporting, Editing, and Publication of Scholarly Work in Medical Journals by The International Committee of Medical Journal Editors.

Participant-level data and statistical code will not be published.

## Discussion

Morning symptoms are common in COPD and have an important impact on patient quality of life (QoL) (7). Nighttime administration may lead to better treatment effects in the morning and thus reduce these symptoms among patients.

In addition to morning symptoms, there is evidence that up to 66% of COPD patients have airway obstruction during their sleep leading to desaturation, poor sleep quality, cardiovascular disease, and more frequent exacerbations (8, 9). A randomized trial with 80 patients showed that tiotropium improved oxygen saturation during sleep compared to placebo (10). The average oxygen saturation during sleep was 3% points higher with nighttime administration and 2% points higher with daytime administration compared to placebo. The difference between the two dosing regimens was not statistically significant; however, only 40 patients were included in this comparison, so it may have been insufficiently powered. Furthermore, this study was not able to examine clinical outcomes such as exacerbations or mortality.

Hospitalization-requiring AECOPD has a significant clinical and socioeconomic impact. A large database review of over 73,000 patients with up to 17-year follow-ups found that fewer than half of patients hospitalized for an exacerbation were still alive after 5 years (11). Patients who survive hospitalization-requiring AECOPD are likely to experience significantly impaired QoL and are at increased risk of further exacerbations. The contribution of non-hospitalized exacerbations to mortality rates (i.e., unreported exacerbations that should have warranted hospital treatment) has not been well-quantified (12). Therefore, COPD treatment to prevent hospitalization-requiring AECOPD or death from all causes is a crucial therapeutic goal for patients with COPD. We will aim to reduce exacerbations and mortality with our simple intervention which can have a great impact on both patients and society, including resource consumption during hospitalizations for this large group of patients.

## Ethics statement

The requirement for ethical approval was waived by the Committees on Health Research Ethics for the Capital Region, due to the nature of the study and the absence of alterations in medication or dosage. The studies were conducted in accordance with local legislation and institutional requirements.
